5.5.2. Blinding

One research coordinator will be designated to maintain and distribute randomization numbers, prepare investigational drugs, and coordinate information among the study staff.

One study physician will be designated for patient management and data recording.
One study nurse will be responsible for administering the investigational product and monitoring safety.

Trained physicians will follow up with patients and perform additional diagnostics.

All members of the research team will remain blinded to each other’s assessments throughout the study.

5.5.3. Investigational Exosome Preparation (Derived from Human Umbilical Cord Mesenchymal Stem Cells)

Exosome nebulization solution: 2 ml/vial, containing 2×10⁹ particles.

The investigational exosome product is provided by Shanghai GenWay Cell & Tissue Storage Co., Ltd. It is derived from mesenchymal stem cells (MSCs) cultured and purified from donated neonatal umbilical cord tissue (see Section 5-0 for donor screening criteria and informed consent form, and Section 5-1 for perinatal tissue handover information). The MSC supernatant is further purified to obtain exosomes.

Informed consent is obtained from all healthy donors. Any remaining investigational products will be uniformly retrieved and destroyed after study completion.

A dedicated management system is established for the storage and distribution of investigational products. Products are delivered directly to designated personnel in the clinical research department by staff from Shanghai GenWay Cell & Tissue Storage Co., Ltd., with proper documentation for product handover.

# 6. Sample Size Requirement

This study is a randomized, placebo-controlled, exploratory clinical trial. A total of 24 subjects will be enrolled at the First Affiliated Hospital of Hainan Medical University, with 12 subjects assigned to the treatment group and 12 to the placebo group.

# Method of Administration, Dosage, Timing, and Course of Treatment for the Extracellular Vesicle (EV) Preparation

**7.1. Registration, Usage Records, Delivery, Distribution Method, and Storage Conditions of the EV Nebulized Solution**

1. After the EV product is fully prepared and passes quality control, laboratory personnel shall complete the **EV Nebulization Application Form** and submit it to the investigators. Both parties confirm relevant information about the EV product (including subject name, hospital admission number, EV product batch number, and quality inspection report), agree on the nebulization schedule, and sign for confirmation.
2. Laboratory personnel shall complete the EV Nebulized Solution Release Application Form, which must be signed by the quality control officer. The form is then submitted to the warehouse manager. Upon reconfirming the relevant EV nebulized solution information (including subject name, hospital admission number, EV nebulization batch number, and quality inspection report), both parties sign the EV Nebulized Solution Release and Handover Form. The refrigerated box containing the EV nebulized solution is then handed over to the laboratory personnel.
3. The laboratory personnel transport the refrigerated box containing the EV nebulized solution to the laminar flow ward. Together with the investigators, they reconfirm the EV nebulized solution information (including subject name, hospital admission number, batch number, and quality inspection report) and sign the EV Nebulized Solution Handover Record Form, after which the solution is handed over to the investigators.
4. **Storage condition:** 2°C–8°C.

**7.2. Dosage and Administration**

Based on results from animal studies, prior volunteer applications, and relevant literature, the administration method is as follows:

Investigational Product

- Name: Human umbilical cord mesenchymal stem cell-derived extracellular vesicle nebulized solution
- Specification: 2 ml: 2×10⁹ particles
- Storage condition: 2°C–8°C
- Dosage and administration: Inhalation twice daily, 2 ml each time, diluted with 6 ml of normal saline and administered via nebulization at 09:00 ± 30 min in the morning and 20:00 ± 30 min in the evening, for a 7-day treatment course.

Placebo Control

- Name: Normal saline
- Specification: 8 ml
- Storage condition: Store below 25°C, avoid direct sunlight, high temperature, or freezing
- Dosage and administration: Inhalation twice daily, 8 ml each time via nebulization at 09:00 ± 30 min in the morning and 20:00 ± 30 min in the evening, for a 7-day treatment course.

To ensure patient safety, the first 4 subjects will be enrolled sequentially. Each subject will be observed for 24 hours after the initial treatment. If no adverse reactions are noted, the next subject will begin treatment. After all 4 subjects have completed the treatment, a safety assessment will be conducted before full clinical trial rollout.

**7.3. Time of Use**

Nebulization is scheduled at 09:00 ± 30 min in the morning and 20:00 ± 30 min in the evening each day.

**7.4. Course of Treatment**

One course lasts 7 days, and it will not be repeated.

# 8 Criteria for Suspension and Termination of the Clinical Study

**8.1. Criteria for Participant Withdrawal or Study Termination**

1. The subject withdraws informed consent and requests to discontinue participation.
2. The subject exhibits significant non-compliance.
3. Occurrence of pregnancy, serious adverse events, death, or loss to follow-up.
4. Use of prohibited concomitant medications.
5. The subject fails to attend scheduled visits.
6. Investigators should make every effort to ensure that each subject completes the follow-up phase, unless discontinuation is clearly in the subject's best interest. Subjects who withdraw from the study should still enter the follow-up phase and will receive periodic follow-ups to monitor survival status until death or the end of the study.

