**5.3. Criteria for Early Withdrawal**

Subjects will be withdrawn from the study if they request to discontinue participation or withdraw informed consent (e.g., due to poor efficacy or adverse events), or are unable to comply with study requirements. Subjects may also be withdrawn at the discretion of the investigator if serious complications or comorbidities, or severe adverse events occur.

The reason for withdrawal must be thoroughly documented. The most recent major efficacy assessment before withdrawal will be used as the final result for statistical analysis. The subject’s CRF (Case Report Form) must be retained for future reference.

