**9.2. Safety Assessment**

Both short-term and long-term safety assessments are included. All adverse events (AEs), including serious adverse events (SAEs), should be monitored and recorded. Detailed records should be maintained for vital signs, clinical symptoms and signs, routine blood tests, urinalysis with pregnancy test, infectious disease screening, blood biochemistry, electrocardiogram (ECG), peripheral oxygen saturation, tumor markers, IL-6, IL-10 levels, immune cell function, and lymphocyte subsets.

1. Short-term (In-Hospital) Safety Monitoring

- Physical examination: including BMI, heart rate, blood pressure, respiratory rate, fingertip oxygen saturation, and complete physical examination.
- Blood tests: including complete blood count (CBC), urinalysis with pregnancy test, infectious disease screening, blood biochemistry, tumor markers, and IL-6, IL-10 levels.
- Auxiliary tests: including ECG and chest HRCT.
- Monitor and record any adverse events during administration of the investigational product. If adverse events occur, follow up with the patient until resolution or end of treatment.

1. Long-term Safety Evaluation

Long-term safety will be evaluated by monitoring the occurrence of adverse events (AEs) or serious adverse events (SAEs) at 6 and 12 months after treatment with extracellular vesicles.

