# 10. Recording Requirements for Adverse Events and Reporting/ Management of Serious Adverse Events

**10.1. Adverse Events (AE)**

1. An AE refers to any untoward medical occurrence in a participant during the course of the study, regardless of its causal relationship with the investigational product. It includes any unfavorable or unintended sign (including abnormal laboratory findings), symptom, or disease temporarily associated with the use of the investigational product, whether or not considered related to it.
2. All AEs, regardless of their relationship to the investigational product, must be recorded in the Case Report Form (CRF), including the diagnosis, onset and duration, interventions taken, treatment interruption status, corrective measures, outcome, and other possible causes.
3. All AEs occurring during the observation period—from the date of informed consent signing to study completion—must be collected, including:
4. Exacerbation of pre-existing symptoms or diseases prior to the trial (excluding the disease intended to be treated by the investigational extracellular vesicles).
5. Increased frequency or severity of pre-existing episodic events.
6. Abnormal changes detected or diagnosed after administration of the investigational extracellular vesicles, even if such abnormalities may have existed before treatment.
7. Not all abnormal lab results or other test findings (e.g., ECG or vital signs) are reported as AEs unless associated with clinical symptoms, result in treatment changes, require medical intervention, or are deemed clinically significant by the investigator. Such findings, if considered part of a clinical diagnosis or corresponding standard medical terminology (reported as an AE), should not be listed separately as AEs but reported as the diagnosis or term (e.g., anemia).

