9. Allergic reactions: For rash or itching: slow infusion or pause; administer 5–10 mg dexamethasone IV and/or 25–50 mg promethazine IM. If symptoms persist or worsen, discontinue nebulization and initiate anti-allergy treatment. For anaphylactic shock: stop nebulization immediately, lay the patient flat, and keep warm. Subcutaneously inject 0.5–1 ml of 0.1% epinephrine; repeat every 30 min if necessary. Administer oxygen therapy; if respiration is inhibited, use mechanical ventilation. For laryngeal edema, perform intubation or tracheotomy. Administer dexamethasone 5–10 mg IV or hydrocortisone 200 mg with 500 ml 5%/10% glucose IV. Use pressor agents like dopamine, norepinephrine, and antihistamines like methylene blue or promethazine IM. For cardiac arrest, initiate CPR and correct acidosis promptly. Closely monitor and document vital signs, urine output, and clinical changes. Patients in critical condition should not be moved.
10. Chills: Administer 25–50 mg promethazine IM during chill episodes.
11. General discomfort: Allow more rest and administer anxiolytics such as diazepam or chlorpromazine as appropriate.
12. All AEs must be followed up until resolution or loss to follow-up. AE resolution is defined as return to baseline health or when the investigator deems no further improvement or deterioration is expected. Follow-up methods may include hospitalization, outpatient visits, home visits, telephone calls, or written communication, depending on severity.

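### Section 8.1 lists a serious adverse event as a ground for withdrawal and afterwards names only survival status for monitoring, so the remaining scheduled safety data of these patients are not secured

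*Protocol*

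**What the plan says.** Two sections of the protocol deal with withdrawal after an adverse event.

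- Section 8.1, item 3, lists "Occurrence of pregnancy, serious adverse events, death, or loss to follow-up". No condition is attached, and the section heading covers both participant withdrawal and study termination.
- Section 5.3 is discretionary: "Subjects may also be withdrawn at the discretion of the investigator if serious complications or comorbidities, or severe adverse events occur".

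Item 6 of section 8.1 describes what happens next. It begins with retention ("Investigators should make every effort to ensure that each subject completes the follow-up phase") and says that patients who withdraw still enter the follow-up phase. It then says that they "will receive periodic follow-ups to monitor survival status until death or the end of the study". It names nothing else to be collected.

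Elsewhere the protocol sets these rules for following AEs:

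- Section 10.1, item 3, has "All AEs occurring during the observation period" collected, from consent to study completion.
- Section 10.6, item 12: "All AEs must be followed up until resolution or loss to follow-up".
- Section 9.2, on in-hospital monitoring: "If adverse events occur, follow up with the patient until resolution or end of treatment". Section 4.3.2, item 2, sets the same limit for AEs during dosing.
- Section 12.2 ties follow-up assessments to the study flowchart.

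Safety is the primary objective (section 2.1). Treatment is short: "One course lasts 7 days, and it will not be repeated".

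**The concern.** Stopping the inhaled product and stopping observation are different decisions, and section 8.1 does not separate them. After D7 no dosing is left to stop. For an SAE after that day, the practical effect of withdrawal is on what is still observed.

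The patients concerned are those most informative for the primary objective. If withdrawal follows an SAE and only survival is then tracked, safety data go missing because of a safety outcome. The Week 12 laboratory and ECG summaries could omit patients who had an SAE, and second or later events in them could go unrecorded. An analysis cannot repair this without assumptions that cannot be checked, because the observations were never made.

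**Working it through.** The protocol gives no SAE rate, dropout rate or power calculation, so it has no figure to reproduce. The check compares the sections and then sizes one lost patient.

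**Step 1. Is withdrawal after an SAE required or optional?** Section 8.1, item 3, states no discretion; section 5.3 does. The terms also differ. Section 5.3 speaks of severe events, and section 10.2 grades severity by CTCAE. Section 8.1 speaks of serious events, which section 10.4 defines separately. The two rules overlap without matching, and nothing says which one governs.

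**Step 2. What is collected after withdrawal?**

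| Section | What it provides | Addresses withdrawn patients? |
|---|---|---|
| 8.1, item 6 | Entry into the follow-up phase; survival status named | Yes |
| 10.1, item 3 | AE collection from consent to study completion | No |
| 10.6, item 12 | Each AE followed to resolution or loss to follow-up | No |
| 4.3.2, item 2, and 9.2 | AEs followed to resolution or end of treatment | No |
| 12.2 | Assessments as marked in the flowchart | No |

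Only 8.1, item 6, addresses these patients, and it names survival alone. The general AE rules can be read as continuing to apply, but 4.3.2 and 9.2 have a different end point from 10.6. Section 10.1 does not say whether study completion means completion of the trial or of that patient's participation.

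**Step 3. What is at risk for one patient?** Take a patient with an SAE on D10 who is then withdrawn. Table 1 still schedules:

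- D28 and D84: vital signs, physical examination and oxygen saturation.
- D84: blood count, urinalysis, biochemistry, tumor markers, IL-6, lymphocyte subsets and ECG.
- D28, D84, D180 and D360: AE/SAE recording.

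Section 10.6 keeps the triggering SAE under follow-up. No section expressly requires the scheduled tests after withdrawal. Recording of new AEs depends on how 10.1 and 12.2 are read.

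**Step 4. Size.** Section 6 gives 12 patients per arm. With k patients of one arm lost to later safety assessment, the share lost is k/12. If none of the remaining n = 12 − k has a later event, the exact one-sided 95% upper limit for the event risk is 1 − 0.05^(1/n).

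| k | Share of arm | n | Upper limit with zero events |
|---|---|---|---|
| 0 | 0% | 12 | 22.1% |
| 1 | 8.3% | 11 | 23.8% |
| 2 | 16.7% | 10 | 25.9% |
| 3 | 25.0% | 9 | 28.3% |

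The loss of precision is modest. The limit also treats the remaining patients as representative, which fails when patients leave because of an SAE. That informative loss is the larger problem, and the table does not measure it.

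**Step 5. Could it arise at all?** The SAE risk p per patient is an assumption here. The chance of at least one SAE in an arm of 12 is 1 − (1 − p)^12:

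- p = 5%: 1 − 0.95^12 = 46%
- p = 10%: 1 − 0.90^12 = 72%
- p = 20%: 1 − 0.80^12 = 93%

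These are chances of an SAE, not of a withdrawal.

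**The case against.** The strongest reply is that the protocol, read as a whole, keeps these patients under observation. Item 6 has withdrawn patients enter the follow-up phase and asks for every effort to complete it. Section 12.2 runs follow-up by the flowchart, and Table 1 marks AE/SAE out to D360. Sections 10.1 and 10.6 contain no exception for withdrawn patients. On this reading, survival monitoring is added to the usual schedule and does not replace it.

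Much of this stands, and it rules out several stronger readings that a reader might infer:

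- **Follow-up is restricted to survival, so all remaining safety data are lost.** The text does not say that survival is the only item, and section 10.6 at least secures the triggering SAE. The supportable statement is that the remaining scheduled data are not secured.
- **Every SAE leads to withdrawal.** Item 3 is a list under a mixed heading, with no word that makes it mandatory, and section 5.3 is discretionary.
- **Nearly all SAE withdrawals would fall after dosing, because 353 of 360 days do (360 − 7).** That is a share of calendar time. It becomes a share of events only if SAE risk is constant over the year, which the document does not support.
- **The product will look safer than it is.** The rule applies to both arms, the triggering SAE is still recorded, and patients with non-serious events stay in the Week 12 summaries. The direction of a between-arm bias cannot be derived.

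The objection does not remove the gap. The one provision written for withdrawn patients names survival and nothing else, and no section says that their scheduled safety tests continue. Section 5.3 also takes the last major efficacy assessment before withdrawal as the final result. That suggests withdrawal is treated as the end of scheduled efficacy assessment.

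**Conclusion.** The point holds as an unreconciled and badly fixed rule on the primary objective. Section 8.1, item 3, does not agree with section 5.3 on withdrawal after an adverse event. Section 8.1, item 6, does not agree with sections 10.1, 10.6 and 12.2 on what is collected afterwards, and sections 4.3.2 and 9.2 add a different limit for AE follow-up. Followed as written, section 8.1 leaves the remaining safety laboratory tests, ECG and oxygen saturation, and possibly new AEs, unsecured in patients withdrawn for an SAE. Missingness would then depend on the safety outcome.

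Each such patient is 8.3% of an arm of 12. The number affected is unknown: it depends on the SAE rate, which the protocol does not give, and on how staff read item 3. The direction of any between-arm bias is also unknown. The conclusion needs neither figure, only that a withdrawal for an SAE is possible under section 8.1. Whether an SAE should lead to withdrawal is a clinical decision and is not judged here.

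**What to change.** 1. Reconcile sections 4.3.2, 5.3, 8.1 (items 3 and 6), 9.2, 10.1, 10.6 (item 12) and 12.2, so that one rule covers withdrawal after an adverse event and one rule covers how long AEs are followed. The withdrawal rule itself is for the sponsor to decide.
2. In section 8.1, distinguish stopping inhalation from ending data collection.
3. In section 8.1, item 6, state that withdrawn patients complete the remaining Table 1 safety assessments and AE/SAE collection through D360 unless they withdraw consent to them.

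The cost is a short amendment and continued visits and calls for withdrawn patients. All of these contacts are already in the Table 1 schedule. The protocol shows no budget, so their cost cannot be stated.

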**8.2. Early Study Suspension or Termination by Investigators**

The investigator should suspend or terminate the study early if any of the following conditions are met:

1. Violation of inclusion criteria or fulfillment of exclusion criteria.
2. The investigator determines that the trial should not continue due to adverse events.
3. Serious safety issues arise during the study (e.g., serious adverse reactions, severe complications, or rapid disease progression).
4. The treatment is found to be ineffective or of low efficacy during the study, lacking clinical value and potentially delaying appropriate treatment.
5. Major flaws are found in the study protocol or significant deviations occur during implementation, making evaluation unreliable.
6. Other reasons deemed necessary by the investigator to suspend or terminate treatment.

# 9. Efficacy Evaluation Criteria

**9.1. Efficacy Assessment**

(1) Primary Efficacy Endpoints

- Clinical symptoms and signs
- Pulmonary function
- High-resolution chest CT (HRCT)
- Frequency and severity of acute exacerbation events

(2) Secondary Endpoints

- 6-minute walk distance (6MWD), including grade and distance
- St. George's Respiratory Questionnaire (SGRQ)
- Leicester Cough Questionnaire
- Modified Medical Research Council Dyspnea Scale (mMRC)

(3) Other Observational Indicators

- Post-treatment changes in IL-6 levels, peripheral blood immune cell function, and peripheral blood lymphocyte subsets.

**9.2. Safety Assessment**

Both short-term and long-term safety assessments are included. All adverse events (AEs), including serious adverse events (SAEs), should be monitored and recorded. Detailed records should be maintained for vital signs, clinical symptoms and signs, routine blood tests, urinalysis with pregnancy test, infectious disease screening, blood biochemistry, electrocardiogram (ECG), peripheral oxygen saturation, tumor markers, IL-6, IL-10 levels, immune cell function, and lymphocyte subsets.

1. Short-term (In-Hospital) Safety Monitoring

- Physical examination: including BMI, heart rate, blood pressure, respiratory rate, fingertip oxygen saturation, and complete physical examination.
- Blood tests: including complete blood count (CBC), urinalysis with pregnancy test, infectious disease screening, blood biochemistry, tumor markers, and IL-6, IL-10 levels.
- Auxiliary tests: including ECG and chest HRCT.
- Monitor and record any adverse events during administration of the investigational product. If adverse events occur, follow up with the patient until resolution or end of treatment.

1. Long-term Safety Evaluation

Long-term safety will be evaluated by monitoring the occurrence of adverse events (AEs) or serious adverse events (SAEs) at 6 and 12 months after treatment with extracellular vesicles.

# 10. Recording Requirements for Adverse Events and Reporting/ Management of Serious Adverse Events

**10.1. Adverse Events (AE)**

1. An AE refers to any untoward medical occurrence in a participant during the course of the study, regardless of its causal relationship with the investigational product. It includes any unfavorable or unintended sign (including abnormal laboratory findings), symptom, or disease temporarily associated with the use of the investigational product, whether or not considered related to it.
2. All AEs, regardless of their relationship to the investigational product, must be recorded in the Case Report Form (CRF), including the diagnosis, onset and duration, interventions taken, treatment interruption status, corrective measures, outcome, and other possible causes.
3. All AEs occurring during the observation period—from the date of informed consent signing to study completion—must be collected, including:
4. Exacerbation of pre-existing symptoms or diseases prior to the trial (excluding the disease intended to be treated by the investigational extracellular vesicles).
5. Increased frequency or severity of pre-existing episodic events.
6. Abnormal changes detected or diagnosed after administration of the investigational extracellular vesicles, even if such abnormalities may have existed before treatment.
7. Not all abnormal lab results or other test findings (e.g., ECG or vital signs) are reported as AEs unless associated with clinical symptoms, result in treatment changes, require medical intervention, or are deemed clinically significant by the investigator. Such findings, if considered part of a clinical diagnosis or corresponding standard medical terminology (reported as an AE), should not be listed separately as AEs but reported as the diagnosis or term (e.g., anemia).

